## Abstract

**Background:**

Scalp acupuncture (SA) and repetitive transcranial magnetic stimulation (rTMS) are effective for treating cerebral infarction. This study aims to examine the efficacy and safety of SA and electromagnetic convergence stimulation (SAEM-CS), which was developed through collaboration between conventional medical physicians and doctors who practice traditional Korean medicine. SAEM-CS was designed to improve function in patients with cerebral infarction, compared to the improvement after conventional stroke rehabilitation, SA, and rTMS therapeutic approaches.

**Methods/design:**

This study is a prospective, outcome assessor-blinded, randomized controlled clinical trial with a 1:1:1:1 allocation ratio. Participants with motion or sensory disabilities caused by a first-time cerebral infarction (*n* = 60) that had occurred within 1 month of the study onset will be randomly assigned to control, SA, rTMS, or SAEM-CS groups. All groups will receive two sessions of conventional rehabilitation treatment per day. The SA group will receive SA on the upper limb area of MS6 and MS7 (at the lesional hemisphere) for 20 min, the rTMS group will receive low-frequency rTMS (LF-rTMS) treatment on the hot spot of the M1 region (motor cortex at the contralesional hemisphere) for 20 min, and the SAEM-CS group will receive LF-rTMS over the contralesional M1 region hot spot while receiving simultaneous SA stimulation on the lesional upper limb area of MS6 and MS7 for 20 min. SA, rTMS, and SAEM-CS treatments will be conducted once/day, 5 days/week (excluding Saturdays and Sundays) for 3 weeks, for a total of 15 sessions. The primary outcome will be evaluated using the Fugl‐Meyer Assessment, while other scales assessing cognitive function, activities of daily living, walking, quality of life, and stroke severity are considered secondary outcome measures. Outcome measurements will be conducted at baseline (before intervention), 3 weeks after the first intervention (end of intervention), and 4 weeks after intervention completion.

**Discussion:**

This study aims to explore the efficacy and safety of SAEM-CS on cerebral infarction. Collaborative research combined traditional Korean and conventional medicines, which can be useful in developing new treatment technologies.

**Trial registration:**

KCT0001768. Registered on 14 January 2016.

**Electronic supplementary material:**

The online version of this article (doi:10.1186/s13063-016-1611-y) contains supplementary material, which is available to authorized users.

## Background

Cerebral infarction (CI) is one of the most commonly reported cerebral vascular diseases, accounting for about 70 % of strokes [1]. The incidence, mortality, and recurrence rates of CI are high, and CI usually leads to serious damage of the central nervous system [2]. Despite a considerable amount of research on effective treatments for stroke, there is still no single intervention that clearly and definitively contributes to stroke recovery. Therefore, stroke treatment strategies should combine multiple disciplines, such as neurology, rehabilitation medicine, and traditional medicine [3]. Scalp acupuncture (SA) is one of several specialized acupuncture techniques, and it involves a filiform needle being used to penetrate specific stimulation areas on the scalp [4]. SA therapy for ischemic and hemorrhagic stroke has been empirically established and is used worldwide [5–8]. The local application of repetitive transcranial magnetic stimulation (rTMS) influences the neural excitability of selected brain areas [9], and it has been reported that low-frequency stimulation (1 Hz) suppresses local neural activities [10, 11], whereas high-frequency stimulation (≥5 Hz) activates local neural activities [12]. Both high-frequency rTMS (HF-rTMS) applied to the lesional hemisphere and low-frequency rTMS (LF-rTMS) applied to the contralesional hemisphere are beneficial for upper limb hemiparesis in patients with chronic stroke [11, 13–17] and in the early phase of stroke [9, 18–20].

Conventional medical physicians and doctors who practice traditional Korean medicine (TKM) tend to focus on each field’s treatment methods in separate medical systems. Unfortunately, efforts to improve the treatment rates of incurable diseases through collaborative research and via the fusion of treatment techniques are lacking. The purpose of this study is to explore the efficacy and safety of SA and electromagnetic convergence stimulation (SAEM-CS), which was developed through a collaborative study between the Department of Physical and Rehabilitation Medicine at Chonnam National University Hospital and the Departments of Acupuncture and Moxibustion Medicine and Traditional Korean Medicine Rehabilitation at Dong-Shin University. Thereafter, we will compare SAEM-CS to conventional stroke rehabilitation, SA, and rTMS therapeutic approaches.

## Methods/design

### Objective

The objective of this study is to compare the efficacy of SAEM-CS on motor function recovery to physical therapy, rTMS, and SA. Further, we aim to explore the synergistic effect of converging SA and rTMS, which are known to be effective in promoting the recovery of motor function, in patients with CI.

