### Study design

This study is a prospective, outcome assessor-blinded, single-center, randomized controlled clinical trial with a 1:1:1:1 allocation ratio. This study is a pilot study to investigate the efficacy and safety of SAEM-CS, which is a newly developed treatment. This study is designed as a single-center study to overcome several procedural and organizational difficulties in terms of developing a research team, since SAEM-CS involves the simultaneous conduction of SA and rTMS. Participants (*n* = 60) who fit the inclusion and exclusion criteria will be randomly allocated into a control group (*n* = 15), SA group (*n* = 15), rTMS group (*n* = 15), and SAEM-CS group (*n* = 15). All groups will receive conventional stroke rehabilitation therapy twice/day, five times/week (excluding Saturdays and Sundays), for a total of 15 times over the course of a 3-week hospitalization period at Chonnam National University Hospital. In addition, the SA group will receive SA therapy, the rTMS group will receive rTMS therapy, and the SAEM-CS group will receive SAEM-CS therapy once/day. Outcome measures will be determined at baseline (before intervention), 3 weeks after the first intervention (end of the intervention), and 4 weeks after completion of the intervention.

This study was approved by the Ministry of Food and Drug Safety (MFDS), Medical Device Clinical Trial Plan Approval number 516. (See Additional file 1.)

The study design is summarized in Table 1 and Fig. 1.

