### Data analysis

Continuous data will be presented as means and standard deviations, while categorical data will be presented as frequencies and percentages. A repeated measures ANOVA will be conducted for the FMA and all secondary outcomes (NIHSS, MBI, FIM, K-MMSE, 9HPT, ASHA-NOMS, FAC, EQ-5D, MAS, Hand Grip Strength, and MEPs). Dependent variables include measured values before and after intervention and the measured values 4 weeks after completion of intervention. An *F* test will be conducted to detect differences between therapies, and Tukey’s post hoc test will be conducted to identify the groups. Repeated contrast tests will be conducted to account for time differences in each group, and the interaction group and time test will be conducted. A *p* value of <0.05 will be considered significant, and participants who drop out of the study will be excluded from the analysis. In brief, only complete case analyses will be used; thus, only subjects who complete the three evaluations will be analyzed. All statistical analyses will be performed using SPSS version 22.0 software (SPSS Inc., Chicago, IL, USA).

Data from participants who engage in less than 70 % of protocol adherence (i.e., receive <10 treatments from 15 trials) will be eliminated. Missing values will be implemented by multiple imputations. In addition, statistical differences will be verified by comparing attribution between eliminated and completed participants to check particular factors causing drop-out.

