## Discussion

This protocol, following the Standard Protocol Items: Recommendations for Interventional Trials (SPIRIT) advice and Consolidated Standards Of Reporting Trials (CONSORT) 2010 guidelines, is designed to explore the synergistic effect of SAEM-CS on the recovery of motor function in patients in the acute stage of CI [36] (Additional file 4). We expect that rTMS will enhance the effect of SA and compensate for a commonly encountered problem in SA treatment: specifically, difficulty in twirling the acupuncture needle (as these needles should be twirled more than 200 times/min).

SAEM-CS is a treatment technique that combines LF-rTMS over the M1 region hot spot (motor cortex at the contralesional hemisphere) and SA stimulation of MS6 and MS7 at the upper limb regions of the lesional hemisphere to promote optimal functioning in patients following stoke. Despite other research showing that HF-rTMS applied to the lesional hemisphere more effectively improves motor function than LF-rTMS applied to the contralesional hemisphere in the early phases of stroke [9], LF-rTMS is selected for the combined SAEM-CS approach because there is some concern about complications that can arise due to the simultaneous use of SA and rTMS in the same hemisphere, and since we cannot completely exclude the interfering effects of HF-rTMS, even with non-magnetic needles. rTMS creates a powerful magnetic field near the stimulated area; therefore, all metal materials must be removed [37]. For rTMS and SA therapies that are conducted simultaneously (during SAEM-CS), we use a KOS-92 non-magnetic steel acupuncture needle that contains a much higher percentage of nitrogen (N) than STS304N1; thus, even in high processing volumes, the needle has no magnetic properties. The same method used in the SAEM-CS approach is employed for the SA and rTMS therapies. Thus, manual stimulation and electroacupuncture are not conducted in the SA group, and LF-rTMS is applied to the contralesional hemisphere in the rTMS group.

In the current study, we select patients hospitalized within 1 month after acute stroke in order to increase the homogeneity of the experimental population. This period was also chosen to increase reliability, because the most important period of recovery falls within the acute and subacute stages of ischemic stroke [38].

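### The exploratory aim of showing synergy between SA and rTMS has no matching test: the named analyses do not isolate the SA x rTMS interaction

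*Protocol article*

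**What the plan says.** Objective (protocol article) sets two aims. The first is comparative: "The objective of this study is to compare the efficacy of SAEM-CS on motor function recovery to physical therapy, rTMS, and SA". The second, introduced as a further aim, is exploratory: "we aim to explore the synergistic effect of converging SA and rTMS". The main Discussion section goes further and says that the protocol "is designed to explore the synergistic effect of SAEM-CS on the recovery of motor function".

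Study design allocates 15 patients to each of control, SA, rTMS and SAEM-CS, all on the same background rehabilitation. On the components, Discussion states: "The same method used in the SAEM-CS approach is employed for the SA and rTMS therapies".

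Data analysis names the tests. "A repeated measures ANOVA will be conducted for the FMA and all secondary outcomes". For the between-group comparison, an F "test will be conducted to detect differences between therapies", and Tukey's "post hoc test will be conducted to identify the groups". Repeated contrasts over time and a group-by-time interaction complete the list. Group is one factor with four levels throughout. The article does not define synergy.

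**The concern.** With arms for neither, SA, rTMS and both, synergy in the usual statistical sense means that the combination exceeds the sum of the separate effects: (SAEM-CS - SA) - (rTMS - control) > 0. That is the SA x rTMS interaction.

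None of the named tests targets this quantity. The F test asks whether any arms differ. Tukey gives pairwise differences. The only interaction named is group by time. If both components work and simply add up, SAEM-CS is expected to beat control and also each single therapy, so such results say nothing about synergy. A stated aim is left without an analysis, and a reader of the results could take a pairwise win for SAEM-CS as support for it.

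**Working it through.** **1. What the sample size rests on.** Sample size gives 40 in total (10 per group) from 4 groups, 3 measurements, f = 0.25, alpha 0.05 and power 0.80, for the time-by-treatment interaction. The article does not state the correlation between visits; 0.5 with sphericity is assumed here.
- lambda = f² x N x m / (1 - rho) = 0.0625 x 40 x 3 / 0.5 = 15
- df = (4-1)(3-1) = 6 and (40-4)(3-1) = 72
- Power = 0.805 at N = 40, and 0.749 at N = 36.

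The figure of 40 reproduces. It is a calculation for group by time, not for synergy.

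**2. Where synergy sits in the named tests.** The 3 group degrees of freedom split into SA, rTMS and SA x rTMS, one each. Crossed with 2 time degrees of freedom, synergy over time is 2 of the 6 in the group-by-time test and is not separated from the other 4. Each Tukey comparison involves two arms; the synergy contrast needs all four.

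**3. What Tukey does when there is no synergy.** Assumptions, none from the documents: SA and rTMS each add 0.6 SD at week 3 and at follow-up, nothing at baseline, and the combination adds exactly 1.2 SD. The SD is that of FMA at one visit, and the correlation rho between visits is 0.5 or 0.8. There are 15 per arm.

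The article does not say whether Tukey is applied to scores averaged over visits or to change, so both are shown.
- Visit-averaged (including baseline): difference (0 + 1.2 + 1.2)/3 = 0.8; SD = sqrt((1 + 2 rho)/3) = 0.816 (rho 0.5) or 0.931 (rho 0.8). Standardised difference: 0.98 or 0.86.
- Week-3 change: difference 1.2; SD = sqrt(2(1 - rho)) = 1.00 or 0.632. Standardised difference: 1.20 or 1.90.
- Tukey threshold: 3.745/sqrt(15) = 0.97 SD of the analysed score.

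Simulation results (repeat runs differ by about one percentage point):

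| Score analysed | rho | SAEM-CS beats control | SAEM-CS beats both single therapies | 2x2 contrast rejects |
|---|---|---|---|---|
| Visit average | 0.5 | 51% | 4% | 5% |
| Visit average | 0.8 | 39% | 2% | 5% |
| Week-3 change | 0.5 | 74% | 7% | 5% |
| Week-3 change | 0.8 | 99% | 32% | 5% |

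True synergy is zero in every row.

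**4. Precision of the 2x2 contrast.** Adjusted for baseline, at 15 per arm:
- SE = 2 x sqrt(1 - rho²)/sqrt(15) = 0.31 SD (rho 0.8) or 0.45 SD (rho 0.5)
- 95% half-width = 2.004 x SE = 0.62 or 0.90 SD.

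**5. Power of the 2x2 contrast.** On an unadjusted change score, in SD of that score:
- SE = sqrt(4/15) = 0.516, against sqrt(2/15) = 0.365 for a pairwise difference
- Power for an excess over additivity of 0.5, 0.8 or 1.0 SD: about 16%, 33% or 48%
- Excess detectable with 80% power: about 1.47 SD.

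**The case against.** Five points can be made for the plan.

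- **Synergy is not the main aim.** A reader of Discussion might infer that it is. Objective puts the comparison first, and Primary outcome ties the FMA to the efficacy of SAEM-CS without mentioning synergy. The F test and Tukey serve that first aim. This stands.
- **No synergy claim from a pairwise win is announced.** A reader might infer that additive effects will be reported as synergy. No section says so, and the trial describes itself as a pilot and exploratory. It is a risk of interpretation, not a stated plan. This stands.
- **The aim is not beyond reach.** A reader might infer that the trial cannot answer the synergy question. All four cells are randomised with the same component methods, so the contrast can be estimated from the planned data. What is lacking is its pre-specification. This stands.
- **The word is undefined.** Discussion speaks loosely of rTMS enhancing SA. If synergy meant only that the combination beats either therapy alone, the Tukey comparisons with SA and rTMS would address it. That is a fair reading, and it is why a definition is needed. Additive effects would also satisfy it, in 2% to 32% of trials in the table.
- **A fuller analysis plan may contain the contrast.** It may, and the point does not claim otherwise. But the article states both the aim and the tests by name, and these do not match. That mismatch is visible without any other document.

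**Conclusion.** The point holds as a mismatch between a stated exploratory aim and the tests named for it. Those tests cannot tell additive from more-than-additive effects. With assumed additive effects of 0.6 SD each and zero synergy, SAEM-CS beats control by Tukey in about 39% to 51% of trials on visit averages and 74% to 99% on week-3 change, while the 2x2 contrast rejects in about 5%. The effect sizes, the correlations and the choice of score are assumptions and move these rates a great deal; the conclusion does not depend on their exact values.

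The point is moderate in weight. It does not affect the validity of the main comparison of SAEM-CS with the other arms.

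**What to change.** Either of two changes, made before the data are analysed.

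1. Keep the aim. Define synergy as more than additive. Pre-specify one exploratory contrast on FMA at 3 weeks, SAEM-CS - SA - rTMS + control, adjusted for baseline FMA and reported as an estimate with a 95% CI. State that pairwise superiority of SAEM-CS will not be described as synergy.
2. Otherwise, remove the word synergistic from Objective and Discussion.

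The first option needs no extra patients, visits or data: one contrast from data already collected, and two sentences. Its drawback is low power (about 33% for an excess of 0.8 SD on an unadjusted change score), so the result should be labelled exploratory and a non-significant contrast should not be read as proof of additivity. The wide interval would show how much, or how little, 15 per arm can say about synergy.

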### Study design

This study is a prospective, outcome assessor-blinded, single-center, randomized controlled clinical trial with a 1:1:1:1 allocation ratio. This study is a pilot study to investigate the efficacy and safety of SAEM-CS, which is a newly developed treatment. This study is designed as a single-center study to overcome several procedural and organizational difficulties in terms of developing a research team, since SAEM-CS involves the simultaneous conduction of SA and rTMS. Participants (*n* = 60) who fit the inclusion and exclusion criteria will be randomly allocated into a control group (*n* = 15), SA group (*n* = 15), rTMS group (*n* = 15), and SAEM-CS group (*n* = 15). All groups will receive conventional stroke rehabilitation therapy twice/day, five times/week (excluding Saturdays and Sundays), for a total of 15 times over the course of a 3-week hospitalization period at Chonnam National University Hospital. In addition, the SA group will receive SA therapy, the rTMS group will receive rTMS therapy, and the SAEM-CS group will receive SAEM-CS therapy once/day. Outcome measures will be determined at baseline (before intervention), 3 weeks after the first intervention (end of the intervention), and 4 weeks after completion of the intervention.

This study was approved by the Ministry of Food and Drug Safety (MFDS), Medical Device Clinical Trial Plan Approval number 516. (See Additional file 1.)

The study design is summarized in Table 1 and Fig. 1.

**Table 1 Tab1:**
[figure not shown]
Treatment schedule and outcome measures

*FMA* Fugl-Meyer Assessment, *NIHSS* National Institutes of Health Stroke Scale, *MBI* Modified Barthel Index, *FIM* Functional Independence Measurement, *K-MMSE* Korean Mini-Mental State Examination, *9HPT* 9-Hole Peg Test, *ASHA-NOMS* American Speech-Language-Hearing Association National Outcomes Measurement System, *FAC* Functional Ambulation Categories, *EQ-5D* European Quality of Life-5 Dimensions, *MAS* Modified Ashworth Scale, *MEP* motor evoked potential, *mRS* modified Rankin Scale

**Fig. 1 Fig1:**
[figure not shown]
Study design flow chart

### Participant recruitment

For achieving adequate participant enrollment to reach target sample size, all stroke patients admitted to the Department of Neurology of Chonnam National University Hospital will be screened by Physical and Rehabilitation Medicine doctors. From among the first-ever patients with CI who are hospitalized and have finished treatment of early acute stage CI at the Department of Neurology, those who are assessed as stable by a neurologist and meet the inclusion and exclusion criteria will be recruited for participation in this study.

Patients who are given an explanation about this study by the Clinical Research Coordinator (CRC) and who voluntarily sign a consent form will be transferred to the Department of Physical and Rehabilitation Medicine to participate in this study (see Additional file 2). The CRC will continuously monitor the medical conditions of enrolled participants to improve adherence to intervention protocols.

### Inclusion criteria

Patients who meet all of the following conditions will be considered for enrollment: patients who are aged >19 years; who have incipient CI confirmed by a computed tomography or magnetic resonance imaging examination; who are diagnosed by a neurologist or neurosurgeon; who experience a CI that resulted in motor and sensory disorders within 1 month of the study onset; who can undergo rehabilitation therapy after hospitalization in the Department of Physical and Rehabilitation Medicine, Chonnam National University Hospital; who have a modified Rankin Scale (mRS) score of 2–4; and who voluntarily sign an informed consent form.

### Exclusion criteria

Subjects whose general condition is not good or fit for SA and rTMS therapies will be excluded. Additional exclusion criteria are as follows: history of brain lesion (e.g., stroke, serious mental illness, loss of consciousness accompanied by head trauma, brain surgery, or seizure disorder); presence of other serious illnesses (e.g., cancer, Alzheimer’s disease, epilepsy, head trauma, or cerebral palsy); transient ischemic attacks; contraindications to electro-magnetic stimulation (e.g., metal implants in the brain, implanted electronic devices in the body, such as non-detachable ferromagnetic metals, metal-sensitive implants less than 30 cm away from the brain like cochlear implants, pacemakers, aneurysm clips or coils, stents, bullet fragments, deep brain stimulation, vagus nerve stimulators, jewelry, or hairpins); continuous convulsion symptoms; previous craniectomy or shunt surgery; elevated intracranial pressure symptoms such as headache, vomiting, nausea, etc.; seizure disorder or epilepsy after CI; history of stroke accompanied by a clear clinical sign; contraindications to SA (e.g., scalp scarring, inflammation from scalp injury, or infection in the treatment region, inability to stop blood flow due to clotting disturbances, such as hemophilia, etc., serious unusual response after acupuncture treatment); women who are pregnant or breastfeeding; patients who disagree with the informed consent; and individuals scheduled for surgery within 2 weeks.

### Ethical considerations

The Institutional Review Board of Chonnam National University Hospital approved this study (CNUH-2015-114; see Additional file 3). The purpose and potential risks of this clinical trial will be fully explained to the patients and their families. All patients will be asked to provide written informed consent before participating in this study.

